# ACTION-1: study protocol for a randomised controlled trial on ACT-guided heparinization during open abdominal aortic aneurysm repair

**DOI:** 10.1186/s13063-021-05552-7

**Published:** 2021-09-19

**Keywords:** Abdominal aortic aneurysm, Open repair, Activated clotting time, Heparin, Vascular surgery, Anticoagulation, RCT

## Abstract

**Background:**

Heparin is used worldwide for 70 years during all non-cardiac arterial procedures (NCAP) to reduce thrombo-embolic complications (TEC). But heparin also increases blood loss causing possible harm for the patient. Heparin has an unpredictable effect in the individual patient. The activated clotting time (ACT) can measure the effect of heparin. Currently, this ACT is not measured during NCAP as the standard of care, contrary to during cardiac interventions, open and endovascular. A RCT will evaluate if ACT-guided heparinization results in less TEC than the current standard: a single bolus of 5000 IU of heparin and no measurements at all. A goal ACT of 200–220 s should be reached during ACT-guided heparinization and this should decrease (mortality caused by) TEC, while not increasing major bleeding complications. This RCT will be executed during open abdominal aortic aneurysm (AAA) surgery, as this is a standardized procedure throughout Europe.

**Methods:**

Seven hundred fifty patients, who will undergo open AAA repair of an aneurysm originating below the superior mesenteric artery, will be randomised in 2 treatment arms: 5000 IU of heparin and no ACT measurements and no additional doses of heparin, or a protocol of 100 IU/kg bolus of heparin and ACT measurements after 5 min, and then every 30 min. The goal ACT is 200–220 s. If the ACT after 5 min is < 180 s, 60 IU/kg will be administered; if the ACT is between 180 and 200 s, 30 IU/kg. If the ACT is > 220 s, no extra heparin is given, and the ACT is measured after 30 min and then the same protocol is applied. The expected incidence for the combined endpoint of TEC and mortality is 19% for the 5000 IU group and 11% for the ACT-guided group.

**Discussion:**

The ACTION-1 trial is an international RCT during open AAA surgery, designed to show superiority of ACT-guided heparinization compared to the current standard of a single bolus of 5000 IU of heparin. A significant reduction in TEC and mortality, without more major bleeding complications, must be proven with a relevant economic benefit.

**Trial registration {2a}:**

NTR NL8421

ClinicalTrials.gov NCT04061798. Registered on 20 August 2019

EudraCT 2018-003393-27

**Trial registration: data set {2b}:**

**Table Taba:** 

Data category	Information
Primary registry and trial identifying number	ClinicalTrials.gov: NCT04061798
Date of registration in primary registry	20-08-2019
Secondary identifying numbers	NTR: NL8421 EudraCT: 2018-003393-27
Source(s) of monetary or material support	ZonMw: The Netherlands Organisation for Health Research and Development Dijklander Ziekenhuis Amsterdam UMC
Primary sponsor	Dijklander Ziekenhuis
Secondary sponsor(s)	N/A
Contact for public queries	[name], MD, PhD [contact] [name]
Contact for scientific queries	[name], MD, PhD [contact] [name]
Public title	ACT Guided Heparinization During Open Abdominal Aortic Aneurysm Repair (ACTION-1)
Scientific title	ACTION-1: ACT Guided Heparinization During Open Abdominal Aortic Aneurysm Repair, a Randomised Trial
Countries of recruitment	The Netherlands. Soon the recruitment will start in Germany
Health condition(s) or problem(s) studied	Abdominal aortic aneurysm, arterial disease, surgery
Intervention(s)	ACT-guided heparinization 5000 IU of heparin
Key inclusion and exclusion criteria	Ages eligible for the study: ≥18 years Sexes eligible for the study: both Accepts healthy volunteers: no Inclusion criteria:
Study type	Interventional Allocation: randomized Intervention model: parallel assignment Masking: single blind (patient) Primary purpose: treatment Phase IV
Date of first enrolment	March 2020
Target sample size	750
Recruitment status	Recruiting
Primary outcome(s)	The primary efficacy endpoint is 30-day mortality and in-hospital mortality during the same admission. The primary safety endpoint is the incidence of bleeding complications according to E-CABG classification, grade 1 and higher.
Key secondary outcomes	Serious complications as depicted in the Suggested Standards for Reports on Aneurysmal disease: all complications requiring re-operation, longer hospital stay, all complications

**Supplementary Information:**

The online version contains supplementary material available at 10.1186/s13063-021-05552-7.

## Background {6a}

Vascular disease, both occlusive and dilating, is a major contributor to mortality and morbidity. Techniques in both open surgery and endovascular treatments have been refined over the past decades, but at present, they are still associated with mortality and high complication rates [1–8]. Since more than 70 years, unfractionated heparin (further: heparin) is used by all vascular surgeons worldwide during open and endovascular non-cardiac arterial procedures (NCAP), preventing arterial thrombo-embolic complications (TEC) [9–11]. The use of heparin also has a major clinical disadvantage: the prolonged clotting time of blood may increase blood loss, lengthens the time needed for adequate hemostasis, and may cause an increase in bleeding complications. Bleeding complications may require blood transfusions or even surgical (re-)exploration in case of extensive and even life-threatening bleeding. Because of the fine line between thrombosis and bleeding, vascular interventions require precise technique and an accurate, optimal level of coagulation. Another major disadvantage of the use of heparin as a periprocedural prophylactic antithrombotic is the fact that heparin has an unpredictable effect in individual patients [12]. The molecular structure of heparin causes a variety of its effect, creating a difference in efficacy not only between different brands, but even between batches of the same brand [13].

In most countries, heparin is administered as a standardized bolus in every patient undergoing NCAP. The most often used dosage is 5000 IU, irrespective of sex, bodyweight, type of procedure, or duration of procedure. Interventional radiologists often use a dose of less than 5000 IU [9, 10].

In all cardiac interventions worldwide, open or endovascular and using cardio-pulmonary bypass or not, the effect of heparin is measured routinely. Many studies have shown that the activated clotting time (ACT) is the preferred test to measure the effect of heparin and that using this test increases the safety of these cardiac interventions [14, 15]. This results in better patient-related outcomes. Surprisingly, vascular surgeons have not adopted this measurement of the ACT during NCAP. This ACT measurement could ensure the individual patient of safe, tailor-made periprocedural anticoagulation [16–23]. This should lead to better results of procedures, with improved patient-related outcomes and less harm for the patient {6b}.

To evaluate the implementation of routine ACT measurements during NCAP, a prospective registry was instituted in 4 major vascular centers in The Netherlands (MANCO, NTR nr. 6973, ClinicalTrials.gov M016-045). All ACT measurements were performed according to a standardized protocol using the same device: Hemostasis Management System Plus (HMS) by Medtronic®, with high-range ACT cartridges (HR-ACT). The percentage of successful measurements was 99% and results were reproducible and comparable between the different hospitals. The validation and standardization of the HMS for ACT measurements are extensively proven in the literature during cardiac interventions [24, 25]. Similar studies were performed with other cartridges (low-range ACT) for the HMS and other brands of ACT measurement systems. Results (on file, manuscript in preparation) show that the HMS and the HR-ACT guarantee the most stable, reproducible, and comparable results during NCAP. Results of the MANCO study, in more than 700 patients, show that ACT measurements can be introduced safely and adequately in daily routine in the operation room and angio-suite, both during open and endovascular NCAP. Evaluation of these data resulted in a safe and adequate protocol to ensure the patient of optimal, ACT-guided heparinization during NCAP. A goal ACT of 200–220 s is considered to be optimal. A systematic review was conducted by our research group, in which only 4 studies could be found that investigated the relation between ACT values and clinical outcomes [26]. Two studies did not find a relationship between ACT value and bleeding complications [19, 23]. Saw et al. found that an ACT > 300 s was associated with increased combined event rate (death, stroke, or MI) in carotid artery stenting [21]. Kasapis et al. found increased bleeding in peripheral endovascular interventions when the ACT was > 250 s [16].

In the MANCO study, the effect of the standardized bolus of 5000 IU was evaluated by measuring the ACT [27]. Results showed that large individual patient variability in the response to heparin was present. The mean baseline ACT in all patients was 129 ± 18 s and the mean ACT 5 min after the initial bolus of heparin was 191 ± 36 s. After the initial dose of 5000 IU heparin, only 33% and 6% of patients reached an ACT of 200 and 250 s, respectively.

Despite the use of heparin, ATEC occurred in 17 patients (9%). The lowest number of ATEC and hemorrhagic complications occurred in the group of patients with an ACT between 200 and 250 s. Conclusions: A standardized bolus of 5000 IU heparin does not lead to adequate and safe heparinization in non-cardiac arterial procedures. Patient response to heparin shows a large individual variability. Therefore, routine ACT measurements are necessary to ascertain adequate anticoagulation. Further research is needed to investigate if heparin dosing based on the ACT could result in less arterial thrombo-embolic complications, without increasing hemorrhagic complications.

The next step was to design a large international multicenter trial to provide level 1 evidence that ACT-guided heparinization will result in less thrombo-embolic complications, without more bleeding complications than unmonitored heparinization with the use of a standardized bolus. This will be evaluated during open abdominal aortic aneurysm (AAA) surgery DSAA classification C: aneurysm originating below the superior mesenteric artery, DSAA being the Dutch Surgical Aneurysm Audit, a Dutch registration that is mandatory for all Dutch vascular surgeons who treat patients with an AAA [28]. In this registry, details are stored regarding indication, techniques, and periprocedural care. The reason to choose open AAA repair for this RCT is that this procedure is subject to standardized care in all hospitals around Europe, also by following the 2019 European Society of Vascular Surgery Guidelines on Management of Patients with an AAA [29].

During a trajectory of 2 years, funding was applied for at ZorgOnderzoek Nederland Medische Wetenschappen (ZonMw, https://www.zonmw.nl) in close collaboration with the Dutch Surgical Association and Dutch Vascular Surgery board. ZonMw’s principal commissioners are the Dutch Ministry of Public Health, Welfare and Sport (VWS) and the Netherlands Organization for Scientific Research (NWO). ZonMw also increasingly works on behalf of other parties, such as local authorities, health funds, health care insurers, private companies, and professional associations. After an extensive (international) peer-reviewed process, a grant of 1.6 million euros was granted for the ACTION-1 trial: ACT-guided heparinization during open abdominal aortic aneurysm repair.

One of the main demands of ZonMw was to execute a pilot study. Results of this pilot study in 46 patients with open AAA repair resulted in a decrease of TEC from 22% in the 5000 IU group to 7% in the ACT-guided group. No increase in bleeding complications or mortality was detected (no mortality in both groups, E-CABG class 1 bleeding in 39% in the 5000 IU group versus 36% in the ACT-guided group) [30, 31]. In the ACT-guided group, the use of protamine at the end of surgery was also described in a protocol [32, 33]. Because of the limited number of included patients, no statistical significance was reached. This underlines the importance of performing a RCT.

## Method/design

This study protocol has been reported in accordance with the Standard Protocol Items: Recommendations for Clinical Interventional Trials (SPIRIT) guidelines [34].

### Study design {8}

The ACTION-1 trial is a multicenter RCT designed to compare the outcomes of ACT-guided heparinization to a standardized bolus of 5000 IU of heparin, during open AAA repair.

Patients undergoing open AAA repair, meeting eligibility criteria, will be included in the trial after giving written informed consent.

The following Dutch vascular centers (academic and large community training hospitals){9} are currently, or in upcoming months, participating in the ACTION-1 trial: Dijklander Ziekenhuis Hoorn, Amsterdam UMC location VUmc, Amsterdam UMC location AMC, Rijnstate Ziekenhuis Arnhem, Elisabeth-TweeSteden Ziekenhuis Tilburg, Isala Ziekenhuizen location Zwolle, Medisch Spectrum Twente Enschede, Maasstad Ziekenhuis Rotterdam, Groene Hart Ziekenhuis Gouda, St. Antonius Nieuwegein, Alrijne Ziekenhuis Leiderdorp, LUMC Leiden, Amphia Ziekenhuis Breda, Haaglanden MC Den Haag, Gelre Ziekenhuizen Apeldoorn, Slingeland Ziekenhuis Doetinchem, Catharina Ziekenhuis Eindhoven, Zorggroep Twente location Almelo, UMCG Groningen.

Also, the University Heart Center Hamburg is in preparation for intended participation. A website solely for the ACTION-1 study has been developed: ACTION-1.nl. All participating hospitals, inclusion, and information for patients (including lay video) are depicted on this website {9} (Appendix).

The study will be single blinded: only the patient will be fully blinded. Furthermore, the Independent Central Adjudication Committee (ICAC) and the data analysts will be blinded for the intervention {17a}. Blinding will follow all legal demands for unblinding in case of patient safety, as deemed as such by attending medical personnel {17b}. Also, the Data Safety Monitoring Board (DSMB) can decide to unblind.

### Study objectives {7}

To establish that ACT-guided heparinization results in safe and optimal anticoagulation during and thereby less complications after open AAA repair. Domain: complications of treatment. The hypothesis is that ACT-guided heparinization will result in a decrease of TEC and all-cause mortality within 30 days after surgery, without a significant increase in bleeding complications when compared to the use of a non-ACT-guided standardized bolus of 5000 IU. The decrease in TEC will lead to less mortality and morbidity, lower number of re-operations, or better patency, all substantially improving patient’s quality of health, efficiency of medical care, and quality of vascular medical care.

### Sample size calculation {14}

In the DSAA (2014 to 2016), the rate of serious complications was 29% for all patients. According to the Society for Vascular Surgery AAA 2018 guidelines, the incidence of TEC is between 15 and 36%. In our preliminary MANCO trial, the incidence of TEC was 14%. For our power calculation, the incidence of TEC is set at 14%. The vast majority of mortality after open AAA repair stems from TEC. A mortality rate of 5% after open AAA repair is derived from DSAA. The hypothesis is that a decrease of TEC will result in a lower mortality of 3%. Bleeding complications derived from the literature and from our MANCO trial and ACTION pilot study are 18–39% (scored according to E-CABG classification) [30].

Derived from data from our pilot study and from literature, the hypothesis is that ACT-guided heparinization will lower the rate of TEC to 8%. The expected incidence for the combined endpoint of TEC and mortality is therefore set at 19% for the 5000 IU group and 11% for the ACT-guided group. Using a continuity corrected chi-square test with a two-sided alpha of 5%, 337 patients are needed in each group to achieve a power of 80%. Including a dropout of 10%, a total of 750 patients are needed for the combined primary endpoints of TEC and mortality.

In our pilot study, no increase in bleeding complications was found for open AAA repair (E-CABG class 1 bleeding was 39% versus 36%). Nevertheless, it is important that excessive bleeding does not occur in the intervention group. Therefore, a non-inferiority calculation was performed. Bleeding complications and TEC are different and have a different impact on patients. Bleeding complications grade 1 E-CABG have less impact on mortality and quality of life than TEC. The expectation is an improvement in combined TEC and mortality of 8%, and the non-inferiority for bleeding complications is set at 11%.

Expecting 32% bleeding complications in the standard group and 33% in the intervention group and a non-inferiority limit of 43% (11% limit difference) with a power of 80% and a one-sided alpha of 5%, 272 patients are required in each group. Therefore, the 750 patients which are needed for the combined primary endpoints of TEC and mortality are sufficient to also evaluate the non-inferiority for bleeding complications.

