## Economic evaluation

### Cost-effectiveness analysis (CEA)

General considerations: We hypothesize that ACT-guided heparinization could lower the rate of TEC and TEC-related mortality to in total 11% and that the quality of life can be increased from 73 to 76%. The economic evaluation of ACT-guided heparinization against standard care with a standardized bolus of heparin will be performed as cost-utility analyses and a cost-effectiveness analysis from a societal perspective with the costs per quality-adjusted life year (QALY) and the costs per prevented complication as the primary economic outcomes. The cost-utility analysis can be used for policy making and composition of a guideline. The cost-effectiveness analysis (CEA) relates to the clinical outcome parameter and may be used for prioritization or benchmarking of strategies that enhance surgical patient safety. The CEA and CUA will be based on a time horizon of 6 months. All related complications are within the time horizon of 6 months and patients will be recovered from the surgery. For on-going complications such as leg amputations, colostomy, permanent neurological deficits, and dialysis, a CEA and CUA with a lifelong time horizon will be made using extrapolation and model-based techniques. For this time horizon, discounting of effects and costs will be performed as stated in the most recent guidelines for cost analysis [36]. To account for uncertainties in the lifelong time horizon, a probabilistic sensitivity analysis will be performed.

Incremental cost-effectiveness ratios will be calculated as the difference in costs per QALY gained and as the difference in costs prevented complications. Sampling variability will be accounted for by bias-corrected and accelerated non-parametric bootstrapping. Results will be reported along with their 95% confidence intervals and displayed graphically with cost-effectiveness planes and with cost-effectiveness acceptability curves. One-way and multi-way sensitivity analyses will be done for the unit costs of the most common complications. Some missing data can be expected; if missing data is at random, this will be handled through multiple imputations with predictive mean matching.

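### The composite event rates add TEC and deaths although the plan attributes most deaths to TEC, so 337 per group does not give the stated 80% power

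*Protocol article*

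**What the plan says.** The section Sample size calculation {14} builds the composite from four inputs. Control-group TEC is fixed first: "For our power calculation, the incidence of TEC is set at 14" per cent. TEC under ACT guidance is then assumed: "the hypothesis is that ACT-guided heparinization will lower the rate of TEC to 8" per cent. For deaths, "A mortality rate of 5% after open AAA repair is derived from DSAA", and ACT guidance is expected to bring this down to 3%. From these the "combined endpoint of TEC and mortality is therefore set at 19% for the 5000 IU group and 11% for the ACT-guided group". The calculation that follows reads: "Using a continuity corrected chi-square test with a two-sided alpha of 5%, 337 patients are needed in each group to achieve a power of 80" per cent. A 10% dropout allowance brings the total to 750.

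The same section says how deaths relate to TEC: "The vast majority of mortality after open AAA repair stems from TEC". It presents the fall in mortality as a result of the fall in TEC. The economic section (Cost-effectiveness analysis) describes the 11% in the same way, hypothesising that ACT guidance could "lower the rate of TEC and TEC-related mortality to in total 11" per cent.

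The two sections that define the primary efficacy endpoint (Main study parameter/endpoint efficacy {12} and Primary efficacy study parameter) describe a single composite incidence, compared between groups by a chi-square test for proportions and reported as an absolute risk difference.

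**The concern.** 19% is 14% + 5% and 11% is 8% + 3%. With a composite scored once per patient, adding the two rates is right only if the two sets of patients do not overlap: either no patient who dies has had a TEC, or the TEC rates already leave out patients who die. The first contradicts the statement that most deaths stem from TEC. The second is stated nowhere. The 14% is presented simply as the incidence of TEC, and the endpoint definition does not exclude fatal events.

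This pair of rates is the sole basis for the 750 patients. If the rates are too far apart, a true effect of exactly the hypothesised size on TEC and mortality will be missed more often than the stated one time in five. Under the hierarchical rule in the Statistical analysis section, a non-significant efficacy result also makes the bleeding non-inferiority analysis exploratory, so lost efficacy power also puts the confirmatory safety conclusion at risk.

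**Working it through.** **Inputs.** From the sample size section: TEC 14% vs 8%; mortality 5% vs 3%; continuity-corrected chi-square test, two-sided alpha 5%, power 80%, equal groups, 10% dropout. The document describes the share of deaths that occur in TEC patients, called f here, only as the vast majority. Any number for f is therefore an assumption, and a range is shown.

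**Step 1: reproduce the plan's figure.** With p1 = 0.19, p2 = 0.11, mean p = 0.15, d = 0.08:

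- Uncorrected: n0 = [1.960·√(2·0.15·0.85) + 0.842·√(0.19·0.81 + 0.11·0.89)]² / 0.08² = 311.5
- Corrected: n = (n0/4)·[1 + √(1 + 4/(n0·d))]² = 336.1, so 337 per group
- Dropout: 337/0.9 = 374.4, so 375 per group and 750 in total

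The plan's numbers reproduce, so the fault lies in the two input rates and not in the calculation after them.

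**Step 2: count each patient once.** Composite = TEC + (1 − f) × mortality. For f = 0.8:

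- Control: 0.14 + 0.2 × 0.05 = 0.150
- ACT-guided: 0.08 + 0.2 × 0.03 = 0.086
- Difference: 0.064

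**Step 3: power at the planned size.** Power = Φ[(d − c − 1.960·SE0)/SE1], with SE0 = √(2p(1−p)/n) for mean p, SE1 = √((p1(1−p1) + p2(1−p2))/n), and c = 1/n with the correction or 0 without. For f = 0.8 and n = 337, SE0 = 0.02485, SE1 = 0.02473 and c = 0.00297. This gives z = 0.498 and power 69.1% corrected; z = 0.618 and power 73.2% uncorrected.

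| Share of deaths in TEC patients (f) | Composite | Difference (points) | Power at 337, corrected / uncorrected | Power at 375, corrected / uncorrected | n per group for 80%, corrected |
|---|---|---|---|---|---|
| 0% (the plan's sum) | 19.0% vs 11.0% | 8.0 | 80.1% / 83.0% | 84.4% / 86.8% | 337 |
| 50% | 16.5% vs 9.5% | 7.0 | 73.6% / 77.2% | 78.4% / 81.5% | 390 |
| 75% | 15.25% vs 8.75% | 6.5 | 69.9% / 73.9% | 74.9% / 78.3% | 422 |
| 80% | 15.0% vs 8.6% | 6.4 | 69.1% / 73.2% | 74.1% / 77.6% | 429 |
| 90% | 14.5% vs 8.3% | 6.2 | 67.5% / 71.7% | 72.6% / 76.3% | 443 |
| 100% | 14.0% vs 8.0% | 6.0 | 65.8% / 70.3% | 70.9% / 74.8% | 459 |

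**Step 4: two other readings of the overlap.**

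- If TEC and death were independent, the composite would be 1 − 0.86 × 0.95 = 18.3% vs 1 − 0.92 × 0.97 = 10.8%. Corrected power at 337 is 76%.
- If the few deaths without TEC were the same in both groups, say 1%, the composite would be 15% vs 9%. Power at 337 is 62.5% corrected and 67.0% uncorrected.

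**The case against.** The strongest defence is that the overlap is not in the document. The inputs come from different sources: TEC from the MANCO study, mortality from the DSAA registry, and the 8% from the pilot and the literature. The pilot had no deaths, so its TEC events were all non-fatal. If the 14% and 8% were meant as TEC in survivors, adding would be correct. That reading is possible, but the text does not state it. If it was intended, the section still has to say so and give the source.

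Second, delivered power depends on the true rates, and 14% is a low input: the guideline range quoted in the same section is 15–36%, and the pilot control rate was 22%. With full overlap and the planned ratio of 8/14, a control TEC rate of 20% (20% vs 11.4%) gives 84% corrected power at 337, and 22% gives 88%. At 15% it is still only about 70%. A higher true rate could therefore offset the error, but the 80% would not then follow from the rates the plan chose.

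Third, the planned analysis does not name the continuity correction, and losses for a 30-day or in-hospital endpoint may be well below 10%. This is fair, and it narrows the gap. With the uncorrected test and all 375 per group analysed, power is 75–78% for 75–100% overlap. It reaches 80% only if about 60% or fewer of deaths occur in TEC patients, which does not fit the plan's own description.

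Fourth, the Data Safety Monitoring Board section says the looks at 100, 200 and 500 patients will provide data for sample size calculations. This mitigates the problem in part, but no method is given and the expected rate to compare against would still be the summed one.

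**Conclusion.** The concern holds. The 19% and 11% are valid only if no TEC patient is among the deaths, and the same section says the opposite. With the named test at 337 per group, any overlap takes power below 80%. How far below depends on a share that the document gives only in words. Reading the vast majority as 80–100% gives 66–69% with the corrected test and 70–73% without it, that is, a type II error of about 27–34% in place of 20%. Even at 50% overlap the figures are 74% and 77%. The finding is that the plan's stated inputs do not support its stated power. It makes no prediction of the power the trial will have if the true TEC rate differs from 14%.

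**What to change.** In Sample size calculation {14}, define the composite rate as TEC plus deaths without TEC, state the assumed share of deaths that occur in TEC patients, and replace 19% vs 11% with the resulting rates. With 80% overlap these would be 15.0% vs 8.6%, labelled as resting on that assumption. Restate the power of 337 per group for the overlap chosen, naming the test: 66–69% corrected or 70–73% uncorrected for 80–100% overlap. If the 14% and 8% were meant to exclude fatal TEC, say so and cite the source instead.

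Carry the correction through to the 19% and 11% in the Abstract (Methods), the 8-point improvement cited beside the bleeding margin in the sample size section, and the 11% in the Cost-effectiveness analysis.

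At the 100- and 200-patient reviews, compare the blinded pooled event rate with the corrected expectation, about 11–12% ((14 + 8)/2 = 11; (15.0 + 8.6)/2 = 11.8), and not with the 15% implied by 19% and 11%.

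The cost is a change of wording and a less favourable stated power. The correction itself requires no extra enrolment, but it does not restore 80% either: that would take 429–459 per group with the corrected test, or about 954–1,020 in total with 10% dropout. Whether to enlarge the trial is a separate decision for the sponsor. The Trial status section reports 90 patients included, so the restatement could be made before the first review at 100.

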### Statistical analysis {20 a,b,c}

Descriptive statistics of continuous variables will be presented as means with standard deviations (SD) or medians with inter-quartile ranges (IQR) depending on the distribution of the data.

Categorical data will be presented as proportions and numbers. The statistical efficacy analysis will be conducted according to the intention-to-treat principle. A separate per-protocol analysis will be performed additionally as a sensitivity analysis. All analyses will be performed with the latest version of the Statistical Package for Social Sciences (SPSS, SPSS Inc., Armonk, NY, USA).

The analysis of primary efficacy and safety outcomes will be performed on an intention-to-treat basis and in a hierarchical fashion. If the statistical analysis shows that there is a statistically significant difference in the primary efficacy endpoint, a statistical analysis of the primary safety study parameter will be performed. If there is no significant difference between study groups in primary efficacy endpoint, assessment of primary safety endpoint will be considered exploratory. Subjects with missing data will be excluded per analysis.

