### Primary safety study parameter

Incidence of bleeding complications according to E-CABG classification, grade 1 and higher [31]. For the bleeding complications, a non-inferiority test will be used. We test the hypothesis that the difference in bleeding between the intervention group and the control group is below the a priori specified boundary of 11%. This will be tested using a one-sided *t* test with an alpha of 0.025, with the null hypothesis that the number of bleedings is above the threshold margin and the alternative hypothesis that is below the threshold margin. If the confidence interval for the bleeding complications does not include the non-inferiority limit in the per-protocol analysis and in the intention-to-treat analysis, non-inferiority for bleeding complications is established.

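### The sample size section calls 750 patients sufficient for bleeding non-inferiority on the strength of a stand-alone calculation, but confirmatory non-inferiority needs efficacy first and then both analysis sets, so its power is below 80%

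*Protocol article*

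**What the plan says.** **Sizing.** Under Sample size calculation {14}, the combined rate of thrombo-embolic complications (TEC) and death is "set at 19% for the 5000 IU group and 11% for the ACT-guided group". A continuity-corrected chi-square test at two-sided 5% then needs 337 per group for 80% power. The total follows: "Including a dropout of 10%, a total of 750 patients are needed". Bleeding is sized on its own, with 32% against 33%, a margin of 11 points, one-sided 5% and 80% power, giving 272 per group. From these two results the section concludes that "the 750 patients which are needed for the combined primary endpoints of TEC and mortality are sufficient to also evaluate the non-inferiority for bleeding complications".

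**Order of testing.** Statistical analysis {20 a,b,c} tests the two primary endpoints hierarchically: "If there is no significant difference between study groups in primary efficacy endpoint, assessment of primary safety endpoint will be considered exploratory".

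**Non-inferiority criterion.** Primary safety study parameter sets the one-sided alpha at 0.025 and requires both analysis sets. If the interval "does not include the non-inferiority limit in the per-protocol analysis and in the intention-to-treat analysis, non-inferiority for bleeding complications is established".

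**Aim.** The abstract's discussion states the goal jointly: "A significant reduction in TEC and mortality, without more major bleeding complications, must be proven with a relevant economic benefit". Study objectives {7} gives a joint hypothesis of the same kind.

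**The concern.** The conclusion that 750 is enough rests on 337 being larger than 272. That comparison covers a single non-inferiority test, in one analysis set, that is always performed. Under the analysis sections, a confirmatory bleeding conclusion needs three results: significant efficacy, non-inferiority in the ITT set and non-inferiority in the per-protocol set. Each added condition lowers the chance of reaching it.

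At stake is how a mixed result will be read. If efficacy is shown but bleeding non-inferiority is not, readers who believe the bleeding question was powered at 80% or more may take the miss as a sign of harm. It could simply reflect limited power under the plan's own assumptions.

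**Working it through.** **Inputs from the sample size section.** Efficacy 19% and 11%, two-sided 5%; bleeding 32% and 33%, margin 11 points, so the expected distance to the margin is 0.11 − 0.01 = 0.10; 10% dropout; equal groups. One-sided alpha for non-inferiority is 5% there and 0.025 in the analysis sections. The efficacy test is continuity-corrected for sizing and a chi-square test with no correction mentioned for analysis, so both are shown.

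**Step 1: reproduce the printed sizes.**
- Efficacy, uncorrected: [1.960·√(2·0.15·0.85) + 0.842·√(0.19·0.81 + 0.11·0.89)]² / 0.08² = 311.6, so 312. The continuity correction, (n/4)·[1 + √(1 + 4/(0.08·n))]², gives 336.1, so 337. This agrees.
- Total: 674/0.9 = 748.9, so 749, against 750 printed. This agrees after rounding.
- Non-inferiority: (1.645 + 0.842)²·(0.32·0.68 + 0.33·0.67)/0.10² = 271.2, so 272. This agrees. At one-sided 0.025 the same formula gives 345.

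**Step 2: power of each test at 337 per arm.**
- Efficacy, corrected: Φ[(0.08 − 1/337 − 1.960·0.02751)/0.02733] = Φ(0.846) = 80.1%. Without the 1/337 term: 83.0%.
- ITT non-inferiority: standard error √(0.4387/337) = 0.03608. Φ(0.10/0.03608 − 1.645) = 87.0% at 5%; Φ(0.10/0.03608 − 1.960) = 79.2% at 0.025.
- At 375 per arm the same formulas give efficacy 84.4% (86.8% uncorrected) and non-inferiority 90.0% at 5% or 83.2% at 0.025.

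**Step 3: efficacy and ITT non-inferiority together.** With independent endpoints the powers multiply.

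| Analysed per arm | One-sided alpha | Corrected test | Uncorrected test |
|---|---|---|---|
| 337 | 5% | 0.801 × 0.870 = 69.7% | 0.830 × 0.870 = 72.2% |
| 337 | 0.025 | 0.801 × 0.792 = 63.4% | 0.830 × 0.792 = 65.7% |
| 375 | 5% | 0.844 × 0.900 = 75.9% | 0.868 × 0.900 = 78.0% |
| 375 | 0.025 | 0.844 × 0.832 = 70.3% | 0.868 × 0.832 = 72.2% |

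**Step 4: add the per-protocol set.** The article gives no per-protocol fraction. I assumed that a random 10, 20 or 30% of the ACT arm is lost, kept the control arm whole, and simulated Wald limits in the two nested sets at 337 per arm. The probability of passing in both sets is then multiplied by the efficacy power of 0.801 (corrected) or 0.830 (uncorrected).

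| ACT arm lost | One-sided alpha | Both sets passed | With efficacy (corrected / uncorrected) |
|---|---|---|---|
| 10% | 5% | 84% | 67% / 70% |
| 20% | 5% | 82% | 65% / 68% |
| 30% | 5% | 78% | 63% / 65% |
| 10% | 0.025 | 75% | 60% / 62% |
| 20% | 0.025 | 72% | 58% / 60% |
| 30% | 0.025 | 69% | 55% / 57% |

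**Step 5: dependence between endpoints.** Latent correlations from −0.3 to 0.5 between TEC or death and bleeding move the joint figures by about 1 to 4 points.

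**The case against.** The strongest reply is that nothing printed is false. Each 80% belongs to its own test, and both are right at their printed alphas. The article never claims 80% for the two together, and at one-sided 5% a stand-alone bleeding test with 337 per arm has 87% power. All of that stands. A reader might infer that the sizing is miscalculated, or that a joint 80% was promised; the article supports neither. What does not stand is the word sufficient, because the non-inferiority test that the article treats as confirmatory is not the stand-alone test that was sized.

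A second reply is that fixed-sequence testing needs no power adjustment, and that missing non-inferiority does not void efficacy. This is correct for efficacy, which is tested first and keeps its full power. The hierarchy does not say that the trial fails if bleeding is unresolved. The abstract's sentence also names major bleeding and an economic benefit, so it is an aim and not a decision rule that these calculations could represent in full. But a sequence that protects the error rate still lowers the chance of reaching its second step.

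A third reply concerns the inputs. Outcomes are 30-day or in-hospital and come from patient files, so losses may be small. The Discussion section expects deviations to be few and equal between groups, which would favour the milder per-protocol scenarios. Per-protocol membership depends on ACT values and on heparin and protamine given, so a random subset is only a convenience. These points are fair, and are why the no-dropout case is shown and the per-protocol figures are labelled as assumptions.

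**Conclusion.** The point holds as a shortfall in power for one conclusion: confirmatory bleeding non-inferiority, and with it the joint aim. For efficacy plus ITT non-inferiority, power is about 70–72% at one-sided 5% and 63–66% at 0.025 with 337 per arm, or 76–78% and 70–72% with all 375. These ITT figures are ceilings for the written rule, because the per-protocol condition can only reduce them. Under the assumed losses, the full rule has about 63–70% or 55–62% at 337 per arm.

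The shortfall does not depend on the conflict between the two stated alphas: it is present at the 5% used for sizing, and 0.025 only enlarges it. It does rest on the plan's event rates and on independence or modest correlation. Very strong positive dependence could bring the joint power up towards that of the weaker test, but no scenario computed reached 80%.

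A reader might also infer that about one trial in three would miss the joint conclusion. That fits 337 per arm at 0.025, or the per-protocol scenarios. For efficacy plus ITT at 5%, the miss rate is 28–30% with dropout and 22–24% without.

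**What to change.** In Sample size calculation {14}, replace the sentence that calls 750 patients sufficient with the power of the rule as written: about 80% for efficacy alone, and the lower figure for efficacy followed by bleeding non-inferiority in both the ITT and per-protocol sets. Compute that figure at the non-inferiority alpha the analysis will use, and state the assumed dropout, per-protocol fraction and independence (or correlation) beside it.

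The cost is one paragraph and a less favourable stated figure. The sample size, tests, margin and hierarchy stay as they are.
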